## 2. OBJECTIVES

### 2.1 Primary objective

The primary objective of the proposed pilot study is to gain insight in the effectiveness of a desk-based lighting device with white light containing ultra-low and safe (according to the IEC62471) doses of artificial UVB irradiation in influencing serum 25(OH)D in the Fall/Winter months. Therefore, an ultra-low and safe daily artificial UVB dose is applied during workdays in the home office over a period of eight weeks (eight hours a day) which leads to the primary research question: **To what extent is an ultra-low (<0.5SED, UVI = ~0.06) and safe daily artificial UVB dose, evenly applied during workdays in a home office over a period of eight weeks (eight hours a day) during autumn, able to sustain the summer serum 25(OH)D levels in healthy office workers?**

We hypothesize that the participants exposed to ultra-low doses of UVB during office hours (while working at home in the home office) will demonstrate a less rapid decline in 25(OH)D levels during the eight-week study period than the control group without UVB supplementation.

### 2.2 Secondary Objectives

As mentioned in the introduction, sufficient 25(OH)D levels also appear essential for optimal daytime functioning (i.e. feelings of energy/vitality) and sleep via its influence on serotonin production during daytime, as well as its influence on melatonin production during the evening and nighttime [17]. Therefore, the secondary objective is to explore the correlations between variations in serum 25(OH)D and indicators of sleep timing, sleep quality and general levels of fatigue.

### 3. STUDY DESIGN

A pilot study with a between-subjects manipulation is proposed for the current study design. The type of light (artificial UVB supplementation vs. no artificial UVB supplementation) is manipulated between subjects. In both the intervention group and the control group, repeated measures are employed during a sampling period of 8 weeks. When possible, randomization over the two groups will be conducted (see section 5.2 for more information). Figure 1 gives a graphical representation of the study design.

[figure not shown]

**Figure 1.** Graphical representation of the study design

For the primary objective, the serum 25(OH)D will be investigated. At the start of the study (day 0), participants will be asked to donate 4 ml blood to determine the baseline 25(OH)D levels in their blood. Subsequently, the light intervention is installed at the desks in the home office of participants in the intervention group delivering the ultra-low dose of UVB during daytime. The control group will not be exposed to artificial UVB radiation and will not receive a lamp at their desk.

The blood sampling and serum 25(OH)D analyses will be repeated in Week 4 and Week 8 on pre-scheduled morning time slots, preferably the same day for all participants, and is conducted by Diagnostiek Voor U (DVU) as a formally recognized health-care provider.

The self-reports on food intake (only vitamin D related), subjective sleep timing and quality, and general levels of fatigue will be investigated through (validated) questionnaires. Both the control and intervention group will receive the questionnaires electronically (via LimeSurvey) in the mornings during which blood sampling is also conducted. The second and third questionnaire contains an option for the participant

to give any comments or feedback about the study (procedure and intervention) to gain some additional insight in their study experience. Table 1 gives an overview of the frequency and timing of the data assessments. These assessments are all conducted in both groups.

**Table 1** Overview of the frequency and timing of the different questionnaires and serum 25(OH)D level measurements

|                                                      | Day 0 | Day 29-31 | Day 58-60 |
|------------------------------------------------------|-------|-----------|-----------|
| General information                                  | X     |           |           |
| Serum 25(OH)D                                        | X     | X         | X         |
| Sleep timing and quality (based on [44 and [45])     | X     | X         | X         |
| General fatigue → Checklist Individual Strength [43] | X     | X         | X         |
| Food intake (vitamin D related), based on [46]       |       |           |           |
| Feedback/comments (optional)                         |       | X         | X         |

### 3.1 Duration of the study

The study protocol consists of a baseline measurement (Day 0 ) and an 8-week intervention period. Three data assessments will be conducted in day 1 of week 0, day 29-31 of week 4 and day 58-60 of week 8. Each data assessment is expected to take about 20-30 minutes. In addition to these three measurement points, participants are asked to complete a short (<1 minute) diary each day about desk presence, time spent outside, and clothing. The study is scheduled for autumn or winter 2020. This season has been chosen as both serum 25(OH)D and outdoor UV intensity start to decline rapidly to negligible values in this period [39,40].

### 3.2 Setting of the study

This study will be performed at the home office setting because of the high frequency of working from home during the COVID19 pandemic. The intervention group will plan a meeting with the lamp technician at the start of the study who will install the lamp in their home office and give explanation about how the lamp works. Blood sampling will be conducted at the DVU location in Eindhoven and questionnaires will be completed at home (online via the secured environment of LimeSurvey).

## 4. STUDY POPULATION

### 4.1 Population base

The population base exists in total of 1612 healthy people living in/around Eindhoven (18+). They will be selected according to the in- and exclusion criteria below (see section 4.2 and 4.3). for the possibility to participate in the study by an independent participant recruitment agency (CG selections). After approval of the criteria via e-mail, eligible participants will be contacted by CG selections via telephone to confirm the in- and exclusion criteria again.

### 4.2 Inclusion criteria

The inclusion criteria include:

- Age over 18 years old
- Fitzpatrick skin type II or III
- Living in/around Eindhoven
- Desk presence (at the home office) of at least 2,5 days per week during the 8 weeks study
- Medically fit to work the hours as contractually agreed
- Finding it no problem to have blood drawn (at Diagnostiek Voor U) three times over a period of 8 weeks

### 4.3 Exclusion criteria

The exclusion criteria include:

- Current pregnancy, breast feeding or a desire to become pregnant
- Having children at home aged 10 years or younger
- Having malignant skin conditions in the past or currently
- Photosensitive medical conditions or photo-sensitising drugs
- Users of medicines and/or cremes mentioning in the prescription as side effect extra sensitivity to the sun / interaction with sun exposure
- Planned use of sun beds, or sunbed use during the past 4 weeks
- Currently taking or planning to take oral vitamin D3 supplements or have been taking D3 supplements during the past 4 weeks.
- High vitamin D levels at the start of the study (>375 nmol/L) which need medical attention [41]

### 4.4 Sample size calculation

In order to estimate whether an ultra-low daily dose of artificial UVB (~0.5 SED) complying to the photobiological safety requirements for general lighting could be effective in raising serum 25(OH)D,

simulations based upon Diffey's model were conducted [42]. The simulation results indicate that when the foreseen intervention dose (0.45 SED) is applied in the optimal conditions (evenly over 8 hours and 20 minutes and 10.5 % body surface area exposure), a maintenance of summer serum vitamin D3 levels could be realized. Figure 2 represents the simulation (Exposure: 0.45 SED; Body Surface Area (BSA): 10.5%, front face (3.5%), 2 x back lower arms (3%), 2 x backside hand (3%), neck (1%)) as well as the effect of such an intervention in the foreseen study timespan of eight weeks. For the study it is expected that at optimized conditions a difference of about 17.6 nmol/L between intervention and control group can be realized in those 8 weeks. Having said that, the expected variance in actual exposure each day will be larger based upon the analysis of variations in exposure duration (desk occupancy) and body surface area exposure. The estimated impact of exposure to a minimum 0.225 SED and a body surface area % minimum of 6.5%) on serum vitamin D3 levels are depicted in Table 2.

[figure not shown]

**Figure 2:** Simulations results conducted to estimate the impact of a 8 week UVB exposure of office workers with input parameters (10.5% skin exposure: front face (3.5%), 2 x back lower arms (3%), 2 x backside hand (3%), neck (1%)). At start: 66.4 nmol/L; End intervention group: 61.7 nmol/L (- 4.7 nmol/L); End Control Group: 44.1 nmol/L (-22.3 nmol/L); Expected intervention effectiveness: +17.6 nmol/L. The UVB dose is evenly (UVI=0.06) given over a period of 8 hours and 20 minutes during the workday. This figure is based on exposure during 5 working days.

**Table 2:** Simulation results for expected serum vitamin D3 levels at reduced body surface area (BSA%) exposure and intervention dose (0.225 SED (50%)).

|                             |                                       | Estimated Serum VitD Intervention Effect (nmol/L) compared to control group |                      |                                              |
|-----------------------------|---------------------------------------|-----------------------------------------------------------------------------|----------------------|----------------------------------------------|
| Variables                   |                                       | Extrapolated Intervention Effect                                            |                      | Extrapolated End-Effect (April)              |
| Daily Exposure (SED) | Body Surface Area Exposure (%) | After 4 weeks                                                        | After 8 weeks | @ minimum of serum VitD control group |
| 0.45                        | 10.5                                  | +12.4 (+23%)                                                                | +17.6 (+40%)  | +32 (+100%)                                  |
| 0.45                        | 6.5                                   | +8.8 (+17%)                                                                 | +13.6 (+31%)  | +20 (+60%)                                   |
| 0.225                       | 10.5                                  | +6.2 (+12%)                                                                 | +8.8 (+20%)   | +16 (+50%)                                   |
| 0.225                       | 6.5                                   | +3.8 (+7%)                                                                  | +5.5 (+12%)   | +10 (+30%)                                   |

These modelling results suggest that ultra-low doses of continuous UVB exposure for eight weeks of use are able to maintain serum 25(OH)D levels in healthy people compared to people who will not receive this exposure (control group). Moreover, the modelling results indicate that the expected differences are in line with effects found in earlier studies [33-38].

A sample size calculation using Gpower was performed assuming that the intervention will reach a (conservative) difference of 8.8 nmol/L between the intervention and the control group (situation 3 in Table 2) at the final measurement point (at 8 weeks). This would mean that the decrease in the control group from baseline to week 8 would be -22.3 while in the intervention group this would be -13.5 (difference of 8.8 nmol/L). The sample size calculation is based on the statistical analysis conducted for the primary objective, namely the difference in serum 25(OH)D between the intervention and control group at the final measurement point, taking into account an alpha of 0.05 and a power of 0.90. The standard deviation within one group is estimated based on a previous similar study which also implemented low-dose UVB exposure to increase serum 25(OH)D in a sample of 20 healthy participants, albeit over a week period using three full-body UVB sunbed sessions [35]. In the post-measurement of this study, they found a significant increase in serum 25(OH)D of 13.9 nmol/L. One month after the end of the UVB intervention they still found a significant increase of 8.8 nmol/L, which is a similar difference we expect in the intervention group compared to the control group. The standard deviation for the power calculation was therefore based on the standard deviation on the difference score found in the sample in this study (similar sample size and similar changes in serum 25(OH)D), namely 8.4 nmol/L. The sample size for detecting a difference of 8.8 nmol/L assuming a standard deviation of 8.4 nmol/L in each group would be 17 participants in each group (see figure 3 below). As we currently only have the availability of 14 lamps, we will choose for 14 participants in each group, and aim to find a larger effect, which is not unlikely when on average, there is somewhat more than 50% desk occupancy and/or if we reach a higher exposure surface area.

[figure not shown]

**Figure 3.** Sample size calculation for change in serum 25(OH)D at 8 weeks

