## 7.2 Randomisation, blinding and treatment allocation

For a full visual overview of the allocation procedure see Figure 6. The independent agency CG selections will make a selection of eligible participants based in the in- and exclusion criteria (see sections 4.2 and 4.3). A list with eligible participants who are interested in participating in the study is mailed to the responsible researcher at the TU/e who will perform block randomization for assignment to the conditions. However, in case insufficient participants are available who work at least 2.5 days at their home office, selection for the intervention group will then be based on presence at the desk (at least 50%). This selection is believed not to influence the primary outcome parameter (25(OH)D serum levels) and as such the conclusions around the primary objective: Participants will not receive any (noteworthy, see [39]) UVB exposure (that could influence the serum 25(OH)D) unless they are allocated to the intervention group. In the statistical analysis, care will be taken to control for potential group differences in desk presence, time spent outside and vitamin D intake by food.

[figure not shown]

**Figure 6.** Allocation procedure

In addition to randomization, blinding is frequently applied to prevent that participants know they are in the control or intervention group. For this specific pilot, only 14 luminaires are available. These luminaires will be placed at the side of the participant's desk when allocated to the experimental group. As such the participant is aware that he or she will receive UVB. Blinding by reducing the sample size to 14 instead of 28 has been considered. However, to prevent that the data can be allocated (identified) to individual persons and to have sufficient power in the study, the total number of participants is estimated to be >25 in total. Since the 25(OH)D levels will not be affected by a pseudo-randomization and non-blinding strategy, it has been chosen to secure privacy of the participants and prioritize a sufficient sample size, and blinding is compromised.

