## 9. STATISTICAL ANALYSIS

The data analyses consist of multiple steps. All data will be presented quantitatively.

As a first step, we will inspect the distribution of the variables of interest. A Shapiro-Wilk test will be conducted to inspect normality of the variables. If needed and possible, a transformation of the scores will be performed to adhere to the assumption related to normality for the statistical analyses. Subsequently, an outlier detection will be performed with outliers determined as values more than 3 SD's from the mean.

Next, we will provide the descriptive statistics for the experimental and control condition for the variables measured only at baseline (see Table 1), as well as for the dependent variables (i.e., the variables for the primary (serum 25(OH)D) and exploratory research objectives (fatigue and sleep), see Section 2.) for each of the measurement points. Comparisons of the variables at baseline will be investigated via independent samples T-test to examine whether there were significant differences between the two groups for any of the variables at measured baseline. If the data appears to be not normally distributed and no transformation is applicable, we will employ a non-parametric test (Mann-Whitney test).

Subsequently, the main research objective (i.e., effects of the light intervention on serum 25(OH)D at week 8) will be investigated using an ANCOVA analyses with the intervention (yes/no) as predictor and change scores in serum 25(OH)D as outcome variable. This analysis will further be controlled for average desk presence and time spent outside. In case data is non-normally distributed a non-parametric test (Mann-Whitney test) will be conducted taking into account the limitation that this analysis cannot control for the mentioned confounders. Analyses will only be conducted with data from participants with both the baseline measurement and the final measurement point available. An alpha level of 0.05 will be used as criterion.

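### The stated 17 per group for 90% power fits only a one-sided test, which section 9 does not declare, and no power is given for the planned 14 per group

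*Protocol*

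**What the plan says.** Section 4.4 of the protocol takes the third scenario of Table 2 as its target: "assuming that the intervention will reach a (conservative) difference of 8.8 nmol/L between the intervention and the control group" at week 8. The standard deviation of 8.4 nmol/L comes from the difference scores of an earlier low-dose UVB study in 20 healthy participants. The error rates are given as "taking into account an alpha of 0.05 and a power of 0.90", with no number of sides, and the section concludes that the number needed, "assuming a standard deviation of 8.4 nmol/L in each group would be 17 participants in each group". The section says that the calculation rests on the primary analysis. Figure 3, which accompanies it, is not shown in the text available.

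The same section then departs from 17 because of the lamp supply: "we will choose for 14 participants in each group, and aim to find a larger effect".

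Section 9 defines the primary analysis as "using an ANCOVA analyses with the intervention (yes/no) as predictor and change scores in serum 25(OH)D as outcome variable", adjusted for average desk presence and time spent outside, in participants with both a baseline and a final value. The criterion is "An alpha level of 0.05 will be used as criterion". No one-sided test is mentioned. The hypothesis in section 2.1 is directional (a slower decline under UVB).

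Section 7.2 explains why blinding was given up in favour of a larger sample. Besides privacy, the reason is "to have sufficient power in the study, the total number of participants is estimated to be >25 in total".

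**The concern.** Section 4.4 ties the sample size to the primary analysis, so both should describe the same test. The 17 matches a one-sided test at 0.05. The group term of an ANCOVA tested at 0.05, with nothing further said, is read as two-sided. As written, the sample size and the analysis disagree.

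Two things depend on this. First, the significance criterion is not fixed: a one-sided p-value of 0.04 in the hypothesised direction would meet one reading and not the other. Second, the only power figure in the protocol belongs to a sample size that will not be used. For the planned 14 per group the reader gets an aim to find a larger effect, without being told how large it must be, and section 7.2 uses power as part of the reason for an unblinded design without putting a number on it.

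**Working it through.** **Inputs (all from sections 4.4 and 9).** Difference 8.8 nmol/L; SD 8.4 nmol/L in each group; alpha 0.05; target power 0.90; allocation 1:1; 14 per group planned; two covariates in the ANCOVA.

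**Method.** Two-sample t-test with the non-central t distribution.

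- Standardised difference: d = 8.8 / 8.4 = 1.048.
- With n per group: df = 2n − 2; non-centrality = d × √(n/2).
- Power = probability that a non-central t variable exceeds the critical value t(1 − 0.05; df) for a one-sided test or t(1 − 0.025; df) for a two-sided test. The opposite tail is negligible here.

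**Step 1: reproduce the plan's figure.** For n = 17: df = 32, non-centrality = 1.048 × √8.5 = 3.054.

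- One-sided: critical value 1.694, power 91.1%. With n = 16 power is 89.4%, so 17 is the smallest n that reaches 90%. The stated figure is reproduced exactly.
- Two-sided: critical value 2.037, power 84.2%. The stated figure is not reproduced.

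**Step 2: the two-sided requirement.**

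- n = 20: power 89.8%.
- n = 21: df = 40, non-centrality 3.395, critical value 2.021, power 91.2%.

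So 21 per group (42 in total) are needed. Removing 2 df for the covariates gives 91.1% at 21, so the answer is unchanged.

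**Step 3: could another two-sided method give 17?** The normal approximation is n = 2 × (z for alpha + z for power)² / d².

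- One-sided: 2 × (1.645 + 1.282)² / 1.0975 = 15.6, so 16.
- Two-sided: 2 × (1.960 + 1.282)² / 1.0975 = 19.1, so 20.

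For the fallback Mann-Whitney test, assuming a relative efficiency of 0.955 or 0.864, the two-sided requirement is 22 or 24. No two-sided variant tried gives 17.

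**Step 4: the planned size.** For n = 14: df = 26, non-centrality = 1.048 × √7 = 2.772.

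| Test | Critical value | Power at 8.8 nmol/L | Difference detectable with 90% power |
|---|---|---|---|
| Two-sided 0.05 | 2.056 | 76.1% (75.8% after 2 df for covariates) | 10.7 nmol/L |
| One-sided 0.05 | 1.706 | 85.4% (85.3% after 2 df for covariates) | 9.5 nmol/L |

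The last column solves for the difference that gives 90% power with n = 14 and SD 8.4.

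**The case against.** The strongest reply is that 17 contains no calculation error. It is exactly right for a one-sided test, the hypothesis in section 2.1 is directional, and Figure 3, which is not shown, may display the number of tails. A contrast between two groups can be tested one-sided, and a separate analysis plan may say so. All of this is fair: the protocol nowhere writes that the test is two-sided, so that reading rests on convention. It does not remove the mismatch. If Figure 3 shows one tail, section 9 still lacks the declaration; if it shows two tails, 17 is wrong. A directional hypothesis does not by itself specify a one-sided test.

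A second reply is that the protocol is open about its limits. This stands. A reader might infer that 90% power is claimed for the planned trial, or that the cut was concealed. The text supports neither: 90% is attached to 17 per group, and the reduction to 14 is explained by the lamp supply with a stated need for a larger effect. That hope is not unreasonable. In Table 2, at 10.5% skin area, the effect is 8.8 at half dose and 17.6 at full dose; assuming linear interpolation, 10.7 nmol/L corresponds to 10.7 / 17.6 = 61% of full dose. What is missing is the number itself.

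A reader might also fault the description of 8.8 nmol/L as conservative, because Table 2 has a lower case of 5.5. The documents do not bear this out as an error: 8.8 is half of the optimised 17.6, and conservative need not mean the worst case. Nor does the protocol say that a non-significant result would be taken as evidence of no effect; it calls the study a pilot and envisages a larger one.

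Finally, the power wording in section 7.2 compares 28 participants with 14 in total and shares its role with privacy. It is loose rather than a claim of 90%, but it is still an appeal to power with no figure behind it.

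**Conclusion.** The point holds as a mismatch between the sample size and the analysis, together with an unstated power for the planned size. On the protocol's own inputs, 17 per group gives 90% power only one-sided. Under the conventional two-sided reading of section 9 it gives 84%, and 21 per group are needed, a shortfall of 4 per group in the stated requirement. The planned 14 per group gives about 76% two-sided or 85% one-sided at 8.8 nmol/L.

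These figures assume SD 8.4 nmol/L in both groups and 14 analysed per group. Covariates that explain variation in the outcome would raise power, covariates that differ between the groups would lower it, and loss of participants would lower it because only those with both measurements are analysed.

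**What to change.** Keep 14 per group and make the sidedness the same in sections 4.4 and 9.

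- **If two-sided:** say so in both sections, replace 17 with 21, and state that 14 per group gives about 76% power at 8.8 nmol/L, with about 10.7 nmol/L detectable at 90% power.
- **If one-sided is intended:** keep 17, declare the one-sided test at 0.05 and its direction in section 9 (also for the Mann-Whitney fallback), and state that 14 per group gives about 85% power at 8.8 nmol/L, with about 9.5 nmol/L detectable at 90% power.

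In either case, replace the appeal to power in section 7.2 with the restated figure. The choice should be recorded before outcome data are seen.

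The cost is protocol wording and a less favourable stated power. No participants, lamps or measurements are added.
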